### Confidentiality

The study will be carried out in accordance with Good Clinical Practice guidance and UK data regulation legislation. All participants will be given an anonymous study ID, which will be used for all data and samples collected. Participants’ personal details will be stored in paper files in a locked office, access to which will be restricted to necessary personnel. Study team members looking at data collected or test results will not be able to see participants’ personal details. All personal information will be destroyed one year following the end of the study.

### Risk in the context of the COVID-19 pandemic

In the context of the COVID-19 pandemic, one potential safety concern is that required two-weekly study appointments may increase the risk of participants being exposed to SARS-CoV-2. A COVID-19 risk assessment has been performed, all study personnel will be instructed and trained in infection control measures and, where possible, social distancing practises will be observed.

### Study timeline

The study activity schedule is outlined in Table 1 and represented schematically in Fig. 1. Baseline data will be recorded on electronic case report forms (eCRFs) and will include demographic information (age, gender, ethnicity), clinical co-morbidities (e.g. diabetes, hypertension, ischaemic heart disease), cardiovascular risk factors (e.g. hypercholesterolaemia, BMI, smoking, family history of cardiac disease), blood test results (e.g. serum haemoglobin, ferritin, urea, creatinine, sodium, potassium, calcium, phosphate, B-type natriuretic protein [BNP], troponin, parathyroid hormone [PTH]), ECG, and echocardiogram results. In addition, we will record pulse rate, blood pressure (average of three readings), weight, presence of oedema, presence of chest crepitations, signs of raised jugular venous pressure, Rockwood clinical frailty score, and E5-QD QoL questionnaire score. The end-of-trial visit will record the same data.

**Table 1 Tab1:** Study activity schedule and procedures

	Screening	C1	C2	C3	C4	C5	C6	C7 or final visit
Week	0	0	Every 2 weeks ±2 days					
Day (approx.)	1	1	3	17	31	45	59	59 or 73
**Informed Consent**								
Informed consent	X							
**Study procedures**								
Targeted physical exam (based on symptoms)	X	X	X	X	X	X	X	X
Vital signs	X	X	X	X	X	X	X	X
Past medical history								
ECG	X		X					X
Concomitant medications	X							
Demographics	X							
Eligibility criteria	X							
A:CR	X							
**Laboratory assessments**								
Baseline blood tests	X							
iSTAT sK	X	X	X	X	X	X	X	X
Lab serum K	X	X	X	X	X	X	X	X
Laboratory safety assessment		X	X	X	X	X	X	X
**Monitoring**								
AE/SAE assessment	Ongoing							
**Drug dosing and monitoring**								
LOKELMA/Placebo		X	X	X	X	X	X	X
RAASi		X	X	X	X	X	X	X
Diuretics use	X	X	X	X	X	X	X	X
**Efficacy evaluations/Other assessments and assays**								
Quality of Life assessment	X							X
Hospitalization assessment		X	X	X	X	X	X	X
HF symptom assessment		X	X	X	X	X	X	X

Table 1—Study schedule of procedures. C6 (i.e. 7 visits total) will occur only in participants not prescribed RAASi at study entry. Baseline blood tests: serum haemoglobin, ferritin, urea, creatinine, sodium, potassium, BNP, troponin, calcium, phosphate, PTH. Laboratory safety assessment: serum sodium, potassium, creatinine

**Fig. 1 Fig1:**
[figure not shown]
Study flow chart. Flow chart demonstrating design of the study. ACEi = ACE inhibitor, ARB = angiotensin receptor blocker, eGFR = estimated glomerular filtration rate, HFrEF = heart failure with reduced ejection fraction, MRA = mineralocorticoid receptor antagonist, OD = once daily, QOL = quality of life, SBP = systolic blood pressure, TDS = three times daily

At initial visit, participants will be initiated on placebo or SZC at initiation dose (i.e. 10 g three times daily). If participants are already taking RAASi medication, they will continue their current medication. If not, the study doctor will start them on appropriate RAASi therapy per local guidance. Participants will be reviewed at 48 h where they will have serum potassium concentration measured and enter the maintenance phase. If serum potassium is 3.5–5.0 mmol/L, participants will begin standard maintenance-dose SZC (i.e. 5 g once daily). For other serum potassium concentrations, and for the remainder of the maintenance phase, dosing will be titrated as outlined in Table 2. If participants experience other adverse effects from RAASi therapy (e.g. symptomatic hypotension, < 90 mmHg recorded systolic blood pressure, postural hypotension), their RAASi dose will be down-titrated if clinically indicated.

**Table 2 Tab2:** IMP dosage protocol

SZC dose at start of visit	Serum potassium at visit	Dose change at end of visit
On 10 g daily	5.0–6.0 mmol/L	Continue 10 g daily
	3.5–5.0 mmol/L	Change to 5 g daily
	< 3.5 mmol/L	Stop
	> 6.0 mmol/L	Stop and initiate rescue
On 5 g daily	> 5.0 mmol/L	Change to 10 g daily
	3.5–5.0 mmol/L	Continue 5 g daily
	< 3.5 mmol/L	Stop
On 0 g daily (i.e. temporary stop)	≤ 5.0 mmol/L	Continue with no IMP
	> 5.0 mmol/L	Initiate 5 g daily

Table 2—Dosage protocol for study visits based on serum potassium measurements. IMP may be restarted two weeks after discontinuation due to hypokalaemia depending on serum potassium result

After screening, recruitment, and randomisation, visits will take place every two weeks (± two days) until the end of the study. The number of visits will depend on participants’ baseline dose of ACEi / ARB / MRA. Patients with no prescribed RAASi at baseline will have seven visits, and others will have six visits.

Following the final study visit, there will be no further follow up visits related to the trial.

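### Table 2 directs rescue for potassium above 6.0 mmol/L only from 10 g daily; at 5 g and 0 g the uncapped rows direct only a step-up in study drug

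*Protocol article*

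**What the plan says.** The Study timeline section of the protocol article sets the dosing sequence. At the first visit "participants will be initiated on placebo or SZC at initiation dose (i.e. 10 g three times daily"), so both arms follow the same blinded dose steps. The next contact is early: "Participants will be reviewed at 48 h where they will have serum potassium concentration measured". If that value is 3.5–5.0 mmol/L, "participants will begin standard maintenance-dose SZC (i.e. 5 g once daily"). Everything else goes to the table: "For other serum potassium concentrations, and for the remainder of the maintenance phase, dosing will be titrated as outlined in Table 2".

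Table 2 has three blocks, defined by the dose at the start of the visit: 10 g daily, 5 g daily, and 0 g daily (a temporary stop).

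- **10 g block.** The upper middle band ends at 6.0 mmol/L, and a separate row above 6.0 reads "Stop and initiate rescue".
- **5 g block.** The top row is potassium above 5.0, with no upper limit: "Change to 10 g daily".
- **0 g block.** The top row is also potassium above 5.0, with no upper limit: "Initiate 5 g daily".

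After the 48 h review, "visits will take place every two weeks (± two days) until the end of the study".

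**The concern.** The 5 g and 0 g blocks are not silent on potassium above 6.0 mmol/L. Their top rows include it and assign it an action, and that action is weaker than the one printed for the same value at 10 g. This is therefore a stated rule and not a detail left out of a condensed article.

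Three features make it worth correcting.

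- A value above 6.0 is severe hyperkalaemia under either threshold the article prints: above 6.0 in the Secondary outcomes list, 6.0 or more in Table 4.
- The 5 g block is not a rare state. It is the standard maintenance dose.
- The trial is placebo-controlled, so a step-up in IMP gives a placebo participant no binder, while RAAS inhibition is being up-titrated in people with CKD who enter with potassium of 5.0–5.5 mmol/L.

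Because the table names rescue in one block, a reader could take its absence from the other two as deliberate. What is at stake is participant safety and uniform conduct, not the statistical comparison.

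**Working it through.** **Reading Table 2 at fixed potassium values.** Each block was read as printed at 5.3, 6.0, 6.1, 6.5 and 7.0 mmol/L.

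| Dose at start of visit | K 5.3 or 6.0 | K 6.1, 6.5 or 7.0 |
|---|---|---|
| 10 g daily | stay on 10 g | stop IMP and start rescue |
| 5 g daily | go to 10 g | go to 10 g |
| 0 g daily | start 5 g | start 5 g |

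Only the 10 g block changes its action at 6.0. Rescue is printed in 1 of 3 dose states.

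**Is it repaired elsewhere in the article?** The word rescue appears nowhere else in the text shown. The only other dose-safety sentence in the Study timeline section concerns other adverse effects of RAASi, with hypotension as its examples, and gives no action for high potassium. No footnote carries the 6.0 rule to the other two blocks. Each block prints a complete set of rows, so damage in text extraction is an unlikely explanation.

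**The 48 h review.** Participants arrive at it on 10 g three times daily, and no block carries that label. The text sends potassium outside 3.5–5.0 to Table 2. The 10 g block is the natural one to use, but the article does not say so.

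**Visit spacing.** Table 1 gives approximate days 3, 17, 31, 45, 59 and 73. The five differences are all 14 days, which agrees with the stated two-week interval.

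**Visits until a printed rescue direction.** Assume potassium is above 6.0 at every visit, only Table 2 is followed, there is no unscheduled visit, and no clinician overrides the table.

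- From 10 g: rescue at the same visit, 0 days.
- From 5 g: 5 g → 10 g → rescue, one visit later, 1 × 14 = 14 days.
- From 0 g: 0 g → 5 g → 10 g → rescue, two visits later, 2 × 14 = 28 days.

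**Range from the ±2 day window.** The article does not say whether the window applies to the interval or to each visit date.

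- Per interval: from 5 g, 14 ± 2 = 12–16 days; from 0 g, 2 × 12 to 2 × 16 = 24–32 days.
- Per visit date (both ends can move by 2 days): from 5 g, 14 ± 4 = 10–18 days; from 0 g, 28 ± 4 = 24–32 days.

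**Primary endpoint.** A responder may have no post-randomisation potassium of 5.6 mmol/L or more. A participant with a value above 6.0 has already failed that condition, since 6.0 > 5.6, so what Table 2 directs next cannot make a participant who completes the study a responder. No sample-size input enters this point.

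**The case against.** The strongest reply is that Table 2 is a dosing table for the study drug. Its title and action column concern IMP dose, and a row that sets the dose does not say that nothing else is done. That stands, and it limits the claim: the table does not forbid treatment.

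Second, the article uses rescue once without defining it, and its sentence on RAASi adverse effects refers to other effects, which suggests that potassium is handled separately. A general rescue rule may well sit in Fig. 1 or the full protocol, neither of which is shown. That possibility stands too. It would not make the printed table consistent, because the table itself directs rescue in one dose state and a lesser step in two.

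Third, 10 g may be the top of a dose ladder: rescue appears there because no IMP step is left. This is a coherent explanation of how the rows arose. It does not help a placebo participant, for whom the remaining steps contain no binder.

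Fourth, the delays rest on stacked assumptions. Table 1 has potassium measured at every visit and adverse-event assessment ongoing, and emergency unblinding is available. The 0 g path is narrower still, since the Table 2 note ties restarting to a stop for low potassium. A stop for potassium above 6.0 at 10 g also leads to 0 g, but the article does not say whether that stop is temporary. This objection stands: the delays are only a bound.

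Fifth, stopping the IMP at 5 g before 10 g has been tried is a separate clinical choice. It could affect later potassium, RAASi escalations, final doses and admissions, which are secondary outcomes. This also stands, so the fix below asks only for rescue.

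A reader might go further and infer that severe hyperkalaemia would go untreated for two to four weeks, or that the trial has no rescue rule for most participants. The documents do not support either. Nothing shown prevents a study doctor from acting, and the places where a general rule would most likely sit are not visible.

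**Conclusion.** The point holds as an inconsistency in the printed table. Above 6.0 mmol/L, rescue is directed from 10 g daily only; at 5 g, the standard maintenance dose, and at 0 g, the printed action is an IMP step-up. It should be fixed as a low-cost safety correction. Confidence is moderate, because Fig. 1 and the full protocol are not shown.

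The 14 days from 5 g and 28 days from 0 g hold only under the four assumptions in the check and should not be quoted as expected delays. The article gives no frequency of potassium above 6.0 at either dose, so expected exposure cannot be stated. No effect on the primary endpoint, the arm comparison or power is claimed.

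**What to change.** - Cap the step-up rows in the 5 g and 0 g blocks at >5.0–6.0 mmol/L.
- Add one rule to Table 2: *serum potassium >6.0 mmol/L at any IMP dose, including the 48 h review: initiate rescue.*
- If Fig. 1 or the full protocol already holds a general rescue rule, align Table 2 with it or refer to it.
- The investigators should decide whether the IMP is stopped, continued or stepped up during rescue at 5 g and 0 g, write that choice into the table, and apply it identically in both blinded arms.

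The cost is two capped cells and one added rule by amendment, plus a briefing of the single-centre study team and the research pharmacy. No sample-size figure changes. The choice on IMP handling is not automatically neutral for the secondary outcomes that depend on later IMP exposure, which is why it should be fixed in advance.

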### Sample collection and analysis

Serum samples will be obtained by venepuncture by one of the research team. Samples for potassium, sodium, calcium, phosphate, urea, creatinine, ferritin, troponin T and BNP testing will be collected into 5 mL SST tubes. Samples for haemoglobin and PTH testing will be collected into 4 mL EDTA tubes. All analysis will be carried out at the NHS South West London Pathology laboratory at St George’s Hospital. With participant consent, serum samples will be saved and stored in a − 80 °C freezer in the Cardiovascular Research Institute at St George’s for the duration of the study.

### IMP and placebo information

The unlabelled study drug (SZC, brand name Lokelma®) or placebo will be provided by AstraZeneca PLC (Cambridge, UK) and delivered to St George’s research pharmacy in bulk. Lokelma® is licensed for use in the UK and European Union for the treatment of hyperkalaemia. The study drug will be labelled upon receipt by an independent company (RenaClinical, Horley, UK) and prepared in accordance with Good Manufacturing Practice and local regulatory guidance.

The study drug will be supplied as a powder for oral suspension in 5 g or 10 g sachets. The entire contents of the sachet should be emptied into a drinking glass containing approximately 45 mL of water and stirred well. The powder does not dissolve, and the tasteless liquid should be consumed while still cloudy. The study drug does not require any special storage conditions, can be taken with or without food, and can be taken with many other medications.

### Outcomes

The main clinical outcome measure will be serum potassium concentration, which will be measured every two weeks, and the dose of RAASi at the end of the study. The statistical outcome measure will be achieving target level of RAASi without hyperkalaemia (i.e. serum potassium ≥5.6 mmol/L). Target RAASi doses are defined as maximum dosing as in Table 3. Outcomes are also displayed in Table 4.

**Table 3 Tab3:** Dose classification of RAASi therapy

	Minimum dose	Half maximum dose	Maximum dose
**ACEi**			
Ramipril	2.5 mg OD	5 mg OD	10 mg OD
Perindopril arginine	2.5 mg OD	5 mg OD	10 mg OD
Enalapril	2.5 mg OD	5 mg OD	10 / 20 / 40 mg OD
Lisinopril	2.5 mg OD	5 / 10 mg OD	20 / 40 mg OD
Perindopril erbumine	2 mg OD	4 mg OD	8 / 16 mg OD
**ARB**			
Losartan	25 mg OD	50 mg OD	100 mg OD
Candesartan	4 mg OD	8 / 16 mg OD	32 mg OD
Irbesartan	75 mg OD	150 mg OD	300 mg OD
Telmisartan	20 mg OD	40 mg OD	80 mg OD
Olmesartan	10 mg OD	20 mg OD	40 mg OD
Valsartan	40 mg BD	80 mg BD	160 mg BD
**MRA**			
Spironolactone	12.5 mg OD	25 mg OD	50 mg OD
Eplerenone	12.5 mg OD	25 mg OD	50 mg OD
**ARNI**			
Valsartan + sacubitril	24 / 26 mg BD	49 / 51 mg BD	97 / 103 mg BD

Table 3—ARNI = angiotensin receptor-neprilysin inhibitor, BD = twice daily, OD = once daily. For analysis and dose titration, participants’ RAASi doses will be classified as low / medium / maximum based on the values in this table. Note—this is not a dose conversion table

**Table 4 Tab4:** Primary and secondary study outcomes

Objectives	Outcome measures	Timepoints of evaluation
**Primary Objective:** To compare SZC vs placebo with respect to:	Enabling participants to achieve target RAASi dose while keeping serum potassium < 5.6 mmol/L.	Blood test for potassium and RAASi dose
**Secondary Objectives:** To compare SZC vs placebo with respect to:	Achieving maximum dose of MRA and ACEi/ARB with serum potassium < 5.6 mmol/L Achieving maximum dose of MRA and ACEi/ARB with serum potasssium < 6.0 mmol/L Time since randomisation to first occurrence of hyperkalaemia (serum potassium ≥5.6 mmol/L) Time since randomisation to severe hyperkalaemia (serum potassium ≥6.0 mmol/L) Number of ACEi/ARB, MRA dose changes Number and durationof hospital admissions during the study Change in serum potassium at respective visits vs baseline	Blood test for potassium and RAASi dose ever two weeks. Other parameters checked at baseline and end of study.
**Tertiary Objectives:**	None	

Table 4—Primary and secondary study outcomes

#### Primary outcomes

Participants will be classified as either responders or non-responders, where a responder is a participant who achieves their target RAASi dose with no post-randomisation serum potassium measurements ≥5.6 mmol/L. Participants who discontinue the study before completion will be deemed as missing.

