### Randomisation

Participants will be randomised 1:1 to either the placebo or active (SZC) arm of the trial. Randomisation is stratified by patients’ baseline RAASi dose at the start of the trial (individuals on < 50% standard dose vs those on ≥50% standard dose) to ensure equal proportions of RAASi therapies in each group.

We will use the REDCap Randomisation Module (https://wiki.uiowa.edu/display/REDCapDocs/REDCap+Randomization+Module). This module can be turned on by selecting the “Enable the randomization module” checkbox during project creation or after. This would preserve the randomisation procedure independent of the study statistician.

Randomisation will be implemented by the research pharmacy at St George’s. Randomisation codes will be generated by the study statistician on an external spreadsheet. The research pharmacy will be informed by the study team as soon the patient is consented, and will use the randomisation list to assign the participant to their allocated arm. In the case of an adverse event or patient safety issue, emergency unblinding will be performed by the on-call research pharmacist.

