#### Secondary outcomes

Responder / non-responder classification, where a responder is defined as a patient who achieved maximum dose of MRA *and* ACEi/ARB with serum potassium ≤5.6 mmol/L;Responder / non-responder classification, where a responder is defined as a patient who achieved maximum dose of MRA and or ACEi/ARB and serum potassium ≤6.0 mmol/L;Time from randomisation to hyperkalaemia (serum potassium ≥5.6 mmol/L);Time from randomisation to severe hyperkalaemia (serum potassium > 6.0 mmol/L);Number of RAASi dose escalations per patient;Final doses of ACEi/ARB, MRA;Change in QoL score, eGFR, ACR, BNP, serum sodium, troponin T at event / end as compared to baseline;Number of hospital admissions per patient, as well as duration of hospital admissions;Within-patient change in serum potassium as compared to baseline;

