#### Sample size estimation

Clinical evidence suggests that the proportion of patients reaching the target dose of RAASi in the control arm would be around 50% as a conservative estimation based on our experience. The study is powered to detect an effect size of the intervention of around 30%.

Group sample sizes of 52 will achieve approximately 90% power to detect a difference between the group proportions of 0.3 using a two-sided Z-test with pooled variance and a two-sided χ^2^ test. The proportion of responders in the placebo arm is assumed to be 0.5 with the corresponding proportion in the active arm 0.8 under the alternative hypothesis. The significance level (α) of the test is 0.05. This results in a total of 104 patients required and, accounting for 20% loss to follow-up, we will recruit 130 patients to be randomised to each group.

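### The primary potassium window opens at randomisation, so a C1 reading taken before the first dose can make a participant a non-responder

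*Protocol article*

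**What the plan says.** Under Primary outcomes, a responder is someone who reaches the target RAASi dose and has "no post-randomisation serum potassium measurements ≥5.6 mmol/L". The window for a disqualifying reading opens at randomisation, and the first dose is not mentioned.

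On timing, the Randomisation section says "The research pharmacy will be informed by the study team as soon the patient is consented", after which pharmacy assigns the arm. Table 1 places consent at screening. Study timeline puts the two-weekly visits after screening, recruitment and randomisation, and says "At initial visit, participants will be initiated on placebo or SZC at initiation dose". The next potassium review is at 48 hours (C2, day 3).

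Table 1 marks potassium at screening and at every visit, C1 included. It marks eligibility criteria at screening only. Eligibility requires the latest serum potassium to be 5.0–5.5 mmol/L.

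Among the secondary outcomes, "Time from randomisation to hyperkalaemia" uses the same 5.6 threshold.

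**The concern.** The upper entry limit is 0.1 mmol/L below the value that fails a participant. If C1 blood is drawn after allocation and before the first sachet, some participants will read 5.6 or more at a moment when neither SZC nor placebo can have had any effect. As worded, the rule has no way back: one such reading settles the primary outcome. The same reading is also an event at or near time zero in the time-to-hyperkalaemia outcome.

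These failures add non-response to both arms and shrink the difference the trial is sized to detect. The sample size section shows no allowance for them: it justifies its 50% control rate by attainment of the target dose and does not mention the potassium condition.

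**Working it through.** **1. The plan's own figure.** Inputs from Sample size estimation: responder proportions 0.5 and 0.8; "The significance level (α) of the test is 0.05"; "using a two-sided Z-test with pooled variance"; "Group sample sizes of 52 will achieve approximately 90% power to detect a difference between the group proportions of 0.3".

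n per arm = [1.96·√(2·0.65·0.35) + 1.2816·√(0.5·0.5 + 0.8·0.2)]² / 0.3² = (1.322 + 0.821)² / 0.09 = 51.01, so 52. Power at 52 is 0.906 by the normal approximation and 0.910 by exact binomial enumeration of the same test. 104 / 0.8 = 130. The stated figures reproduce.

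**2. Order of events.** Consent is at screening; pharmacy is told at consent and allocates; visits follow randomisation; C1 includes a potassium sample and the first dose; the next potassium is at 48 hours. Read together, these make a post-randomisation, pre-dose C1 value possible. No sentence fixes the order of draw, allocation and first dose, so this is an inference.

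**3. Share of participants affected.** The protocol gives no repeat-measurement SD, so s is an assumption. Take the qualifying value m as uniform on 5.0–5.5 (also an assumption) and C1 as m plus normal variation with SD s. The share is the average over m of 1 − Φ((c − m)/s), with c = 5.6 for unrounded values and c = 5.55 if C1 is reported to 0.1.

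| Assumed s (mmol/L) | Unrounded | Rounded to 0.1 |
|---|---|---|
| 0.08 | 0.8% | 2.6% |
| 0.10 | 1.7% | 4.0% |
| 0.20 | 7.9% | 11.4% |
| 0.30 | 14.7% | 18.5% |

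**4. Effect on power.** If a share q of each arm fails at C1, independently of what would otherwise have happened, the rates become 0.5(1 − q) and 0.8(1 − q).

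| q | Rates | Difference | Exact power, 52 per arm | n per arm for 90% power (normal approximation) |
|---|---|---|---|---|
| 0 | 0.500 vs 0.800 | 0.300 | 0.910 | 52 |
| 2% | 0.490 vs 0.784 | 0.294 | 0.895 | 55 |
| 5% | 0.475 vs 0.760 | 0.285 | 0.870 | 60 |
| 10% | 0.450 vs 0.720 | 0.270 | 0.827 | 68 |
| 15% | 0.425 vs 0.680 | 0.255 | 0.780 | 78 |

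This takes 0.5 and 0.8 as rates that contain no C1 failures. If the planners had already allowed for such failures, the loss would be counted twice; the text does not say.

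**The case against.** The timing is inferred. If allocation came after the C1 sample, that value would not be post-randomisation and the problem would vanish. This stands as a caveat, but the text points towards allocation first, and the primary endpoint should not depend on an unstated order.

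Screening and C1 are both at about day 1, and potassium is measured at screening. A C1 value close in time to the qualifying one should differ from it mainly by short-term and assay noise, which favours the top two rows of the first table and a small loss. This also stands: a share of 10–15% needs an SD of about 0.2–0.3.

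A C1 value of 5.6 or more might be thought to make the participant ineligible. Eligibility is marked at screening only, however, and a participant already allocated stays in the intention-to-treat analysis.

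A reader might also infer a stronger point from Table 1, which lists an iSTAT and a laboratory potassium at every visit: that either reading can fail a participant, adding failures unrelated to treatment in both arms. The protocol does not support this. It never says that either assay counts. Sample collection and analysis sends all analysis to the pathology laboratory, and the choice of assay is detail that an article may leave to the full protocol. Nor would the extra failures fall equally. With assumed between- and within-person SDs of 0.2 each, laboratory error SD 0.08, iSTAT error SD 0.10–0.20 and five post-dose visits, counting either assay adds 6–16 percentage points of failure at a mean potassium of 5.1, but only about 1–5 at 4.8. If SZC lowers potassium, the additions fall mainly on placebo and could widen the difference.

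**Conclusion.** The point holds for the C1 reading. The rule as worded can fail participants on a value that neither arm could have influenced, and it puts early events into time to hyperkalaemia for the same reason. The effect is dilution. A reader might infer bias, but allocation is randomised and the C1 value is untouched by treatment, so such failures are expected equally in both arms.

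The size is uncertain because the protocol gives no repeat-measurement SD. At an SD of 0.08–0.10 the share is about 1–4% and exact power stays at about 0.88–0.90. At 0.2–0.3 the share is about 8–18.5%, and power is already down to 0.83 at a 10% share and 0.78 at 15%. The larger losses are therefore possible but not established. The stated sample size is arithmetically correct. The two potassium assays are not a defect on this evidence.

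**What to change.** Define the responder as a participant who reaches the target RAASi dose with no serum potassium of 5.6 mmol/L or more measured after the first dose of study drug, including values found between scheduled visits, for example during an admission. Limiting the rule to scheduled visits would drop hyperkalaemia that the present wording captures. State the order of C1 sampling, allocation and first dose. Start the potassium window of secondary outcomes 1–4 at the same point, so that a pre-dose C1 value is baseline information and not an event. Naming the laboratory value as the endpoint assay would be a useful clarification, no more.

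The cost is a short wording change to the primary and four secondary definitions, with no new data and no change to the planned 52 per arm. The one downside is that the window then opens at first dose and not at randomisation, so participants who are randomised but never dosed need a stated handling rule under intention to treat, fixed before unblinding.
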